## Methods/design

### Study design

The clinical trial is exploratory and will follow a 2-period double-blind cross-over design. The allocation ratio will be 1:1. It will take place at the Chronic Disease Innovation Centre (CDIC) at Seven Oaks General Hospital in Winnipeg, Canada. The study protocol flow chart is shown in Fig. 1. This trial will be conducted in compliance with Good Clinical Practice (GCP) and all local and national guidelines.

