**Fig. 1 Fig1:**
[figure not shown]
Study protocol flow chart

Participants will consent to follow a 26-week study regimen. Each participant will receive 2 sachets per day containing either 15 g of RPS (MSPrebiotic, resistant potato starch treatment) or 15 g cornstarch (Amioca TF, digestible starch control). The powder in the sachets will be mixed in water and consumed, one sachet in the morning and one before bed. Participants will be instructed to consume the investigational product at least 2 h prior to or after taking any medication.

For the first 2 weeks, participants will go through a run-in period, where they will all receive the cornstarch control. During weeks 3 to 12 (period 1), participants will receive either RPS or cornstarch. The first treatment received will be determined by a randomization procedure. During weeks 13 to 16, participants will undergo a washout period where they will all consume cornstarch. During weeks 17 and 26 (period 2), participants will receive the treatment they did not previously consume (RPS or cornstarch, respectively).

Participants will complete questionnaires and food records at the beginning and end of each treatment period (Table 1). They will also provide blood, urine, and faecal samples for analysis (Table 1).

**Table 1 Tab1:** The schedule of enrolment, interventions, and assessments

Assessment	Screening and enrolment	Visit 1	Visit 2	Visit 3	Washout	Visit 4	Visit 5
Periods		Run-in		Period 1		Period 2	
Day in study		1	15	84	85–112	113	182
Informed consent	□						
Screening	□						
Demographics	□						
Medical history anthropometrics	□	□	□	□		□	□
Dietary recalls			□	□		□	□
SF-36, ESAS			□	□		□	□
Blood, urine, and stool collections			□	□		□	□
Adverse event			□	□		□	□

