### Statistical analysis

The bioinformatics and statistical analyses of microbiome data will be performed with the assistance of Microbiome Insights and the Data Science platform at CHI; it will be updated based on the recommendations and technology advancements between now and the processing of the samples. In general, the default settings of the FLASH assembler [22] will be used to merge the overlapping paired-end Illumina fastq files. UPARSE algorithm [23] will be used for (a) quality filtering of the reads based on the maximum expected error value = 1.0, (b) identification of unique sequences, (c) abundance sorting and removal of singletons, (d) clustering the reads into operational taxonomic units (OTUs) based on 97% identity threshold, (e) de novo and reference-based chimera checking (against GOLD database [22]), and (f) construction of OTU table. Taxonomic classification will be then carried out using QIIME [26] implementation of UCLUST [24] and will be aligned against the Greengenes database using the PyNAST algorithm [25]. Phylogenetic trees were built with FastTree [27] for further comparison between microbial communities. Prior to performing downstream analyses, the resulting OTU table will be filtered to remove all the samples with low-sequencing depths. Community richness and diversity indices will be then calculated using QIIME at a given even depth per sample. Phylogenetic- (weighted UniFrac distances) and abundance-based (Bray-Curtis dissimilarity) β-diversity metrics will be calculated following normalization of the final OTU table using the cumulative sum scaling (CSS) transformation [28]. Principal coordinate analysis (PCoA) will be applied on the resulting distance matrices to generate two-dimensional plots using default settings of the PRIMER-6 software (PRIMER-E Ltd, Plymouth). Unsupervised clustering analysis will be performed to relate clustering patterns of samples to the proportion of the core OTUs within each niche (core OTUs defined as those present in at least 75% of samples in each niche). The relative abundances of the selected OTUs will be normalized across samples. Bray-Curtis dissimilarities will be calculated using the R “vegan” package [29], and the resulting matrix will be subjected to unsupervised hierarchical clustering using the R “dendextend” package [30] and will be visualized over the heatmap of abundance matrix using the R “complexheatmap” package [31]. The UNIVARIATE procedure of SAS will be used for testing the normality of residuals for α-diversity measurements. Non-normally distributed data will be either log or Box-Cox power transformed and then subjected to analysis of variance (ANOVA) test using MIXED procedure of SAS. All pairwise comparisons among the groups will be tested using Tukey studentized range adjustment. Permutational multivariate analysis of variance (PERMANOVA; implemented in the Primer6 software) will be used to detect significant differences between β-diversity metrics of microbial communities. The relative abundances of selected core OTUs will be tested for statistically significant associations with available metadata using multivariate analysis with linear modelling (MaAsLin) [32] accounting for all potential confounders (covariates) that could be associated with the profile of microbiome (i.e. sex, age, BMI) and participants (treated as a random factor). Significant associations will be considered below a *q*-value threshold of 0.1. To assess the shifts in functionality of microbiome, correlation network analysis (CoNet, [33]) will be used to explore microbial co-occurrence/mutual-exclusion relationships and identify hub OTUs that show the highest number of positive/negative correlations with other OTUs under treatment conditions.

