
Effects of treatment on linear outcomes at the end of each period will be analysed by the SAS MIXED (SAS 9.4) procedure. Sequence and sex will be included in the model as fixed factors, and participants will be included as a repeated factor. The normality of the data distribution will be done using the Shapiro-Wilk test, and the non-normal variables will be transformed prior to analysis. Demographic data will be reported as the mean ± standard deviation. The results will be reported as least-squared means ± standard error of the mean (SEM) unless otherwise specified. Statistical significance will be set at *p* < 0.05 for all analyses. The Data Science Platform in CHI will provide data management support in addition to biostatistics support for the project.

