### Randomization, blinding, and code-breaking

Eligible patients (*n* = 36) will go through assessments at baseline and will be randomly allocated to 2 groups, each consisting of 18 participants. Randomization will be done by an independent researcher in the biostatistics platform at the George and Fay Yee Centre for Healthcare Innovation (CHI) at the University of Manitoba. Randomization will be performed using code written in the R statistical programming language (version 3.5.3). Treatments will be assigned with a 1:1 ratio. A total of 48 randomization cards will be prepared, one set of 24 for each sex. The randomization schedule will be transferred into sets of opaque sealed envelopes. After a participant’s baseline visit, the study staff will open a sealed envelope which will contain the participant’s allocation. The order of the interventions will be blinded for both the investigators and the participants. Treatments will be given in sealed sachets; sachet content will be blinded by an outside party, given to the study staff labelled as A or B, and dispensed to participants according to their treatment period. Treatments will not be unblinded until the analyses are complete, unless required due to adverse events during the clinical trial. There will also be a midpoint review of the participants’ clinical data by an independent nephrologist who will be unblinded (see the “Qualified investigator responsibilities” section).

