### Sample size calculation

A final samples size of 30 participants in this study will be able to detect a difference between the treatments in total p-cresol sulphate of 17.5 μmol/L, or ~ 15% change, at a power of .88 (alpha = 0.05, two-sided), given a within-person correlation of .79 [23] and an estimated standard deviation of 45 μmol/L [9] for total p-cresol sulphate. A 30% or greater drop in uremic solutes would be considered clinically significant, warranting additional trials investigating this prebiotic intervention in CKD, and we are confident we would be able to detect such a change should it occur. To account for the loss of power due to dropouts, we will recruit 36 participants.

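### The stated crossover model has no period term, so a shift in toxins between days 84 and 182 costs power and biases the estimate if completers are unequal by sequence

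*Protocol article*

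**What the plan says.** The Study design section says that the trial "will follow a 2-period double-blind cross-over design". Under Randomization, blinding, and code-breaking, participants "will be randomly allocated to 2 groups, each consisting of 18 participants". In period 2, according to the text below Fig. 1, "participants will receive the treatment they did not previously consume".

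The Statistical analysis section sets out the model for continuous outcomes in two sentences. The first is "Effects of treatment on linear outcomes at the end of each period will be analysed by the SAS MIXED (SAS 9.4) procedure". The second is "Sequence and sex will be included in the model as fixed factors, and participants will be included as a repeated factor". Period appears there only as the time of measurement. Nowhere does the article fit a period effect, or a sequence-by-treatment term, which would be equivalent in a design with two sequences and two periods.

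In the same section, the MaAsLin model for core OTUs is described as "accounting for all potential confounders (covariates) that could be associated with the profile of microbiome (i.e. sex, age, BMI"), with participants as a random factor. Period is again absent.

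**The concern.** In a 2×2 crossover each participant is compared with themselves across two occasions, so the main nuisance effect within a person is anything that differs between those occasions. Sequence and sex differ only between people and cannot absorb it. Treating participant as a repeated factor models the covariance of the two values; it does not fit a mean difference between periods.

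A period shift is plausible here. Table 1 puts the two period ends at days 84 and 182. Participants must have an eGFR below 15 and not be on dialysis. The Background section says that these toxins build up as kidney function falls. If toxin levels rise between the period ends, that rise makes RPS look better in those who took it first and worse in those who took it second. With equal numbers the two errors cancel in the mean but remain in the residual variance. With unequal numbers part of the rise enters the treatment estimate.

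**Working it through.** **Inputs from the article.** Final n = 30 of 36 recruited, 18 randomised per sequence, target difference 17.5 μmol/L in total p-cresol sulphate, SD 45, within-person correlation 0.79, two-sided alpha 0.05, stated power 0.88.

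**Assumption.** Drift is the mean change from day 84 to day 182 that is unrelated to treatment. The article gives no value. I use 5 to 20 μmol/L. Since 17.5 is described as about 15%, the implied mean is 17.5/0.15 ≈ 117, so this range is about 4% to 17% of the mean.

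**Step 1: the plan's own figure.** SD of the within-person difference = 45 × √(2 × (1 − 0.79)) = 29.16. Noncentral t with n = 30 and 29 df gives power 0.888, which reproduces the stated 0.88. With period fitted (28 df) it is 0.887.

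**Step 2: what happens without period.** Let τ be the effect of RPS minus control. The within-person difference has mean τ − drift in those given RPS first and τ + drift in those given control first. The model without period in effect averages all 30 differences, so:

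- bias = drift × (n control-first − n RPS-first)/30
- at 15/15, the expected variance of the differences = 29.16² + drift² × 30/29

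At 15/15 the SD therefore rises from 29.2 to 29.6, 30.9 and 35.6 at drifts of 5, 10 and 20.

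**Step 3: power at 15/15.** The offset is a fixed ± amount and not random normal error, so power was simulated.

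| Drift (μmol/L) | Power, period omitted | Bias |
|---|---|---|
| 0 | 0.89 | 0 |
| 5 | 0.88 | 0 |
| 10 | 0.86 | 0 |
| 15 | 0.83 | 0 |
| 20 | 0.78 | 0 |

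With period fitted, power stays at about 0.89 throughout. Type I error without period falls to 0.038 at drift 10 and 0.017 at drift 20, so the test is conservative.

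**Step 4: unequal completers.** Suppose six of the 36 drop out at random, with C(36,6) = 1,947,792 possible sets.

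| Split, either way | Probability | Bias/drift | Bias at drift 10 to 20 (μmol/L) |
|---|---|---|---|
| 15/15 | C(18,3)²/C(36,6) = 34% | 0 | 0 |
| 16/14 | 2·C(18,2)·C(18,4)/C(36,6) = 48% | 2/30 = 0.067 | 0.7 to 1.3 |
| 17/13 | 2·18·C(18,5)/C(36,6) = 16% | 4/30 = 0.133 | 1.3 to 2.7 |
| 18/12 | 2·C(18,6)/C(36,6) = 1.9% | 6/30 = 0.2 | 2.0 to 4.0 |

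The expected absolute bias is 0.48 × 0.067 + 0.16 × 0.133 + 0.019 × 0.2 ≈ 0.057 × drift, about 0.6 to 1.1 μmol/L for drifts of 10 to 20.

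The sign depends on which sequence loses more people. In the extreme case at drift 20, a true −17.5 is estimated as −21.5 with 18 RPS-first and 12 control-first. With the split reversed it is −13.5, and power is 0.53 against 0.87 with period fitted. Type I error at 18/12 stays at about 0.05 (highest simulated value 0.055).

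**Step 5: does sequence absorb the shift?** No. Mixed models with treatment, sequence and sex were fitted to simulated data at drift 20 (150 data sets per split). At 15/15 the mean standard error was 6.42 without period and 5.18 with it. At 18/12 the mean estimate was −21.1 without period and −17.0 with it (truth −17.5).

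**The case against.** The list of factors is not complete as written: it leaves out treatment too, although the preceding sentence makes clear that treatment is estimated. This is a condensed article, the full model code may sit in an analysis plan that is not shown, and the trial is described as exploratory. It is therefore fair to say that the text does not prove period will be omitted. But the authors did name factors, chose two that do not vary within a person, and left out the standard one that does. An analysis plan that added period would be extending a published list, so the wording needs correcting.

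The objections on size largely stand, and several stronger readings should be resisted:

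- **Bias of 2 to 4 μmol/L (11% to 23% of the target).** A reader might take this as typical. It needs all six planned dropouts to come from one sequence. Under random dropout, 15/15 or 16/14 has 82% probability. Dropout related to sequence could raise the odds of imbalance, but nothing in the article indicates it.
- **A larger power loss.** Putting the inflated SD into a noncentral t gives about 0.85 and 0.74 at drifts of 10 and 20. That treats a fixed offset as normal error; simulation gives 0.86 and 0.78.
- **Drift over the whole 26 weeks.** The analysed values are 98 days apart.
- **False positives, or a missed important effect.** Type I error is not materially raised. For the 30% drop that the article calls clinically significant (about 35 μmol/L), power stays at about 0.999 or higher at drift 20, even at 18/12.
- **PERMANOVA.** The article says only that "Permutational multivariate analysis of variance (PERMANOVA; implemented in the Primer6 software) will be used to detect significant differences" and does not mention participant. That is silence about model structure in a condensed account, in a section that says the microbiome methods will be updated. It does not show that the pairing will be ignored.

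**Conclusion.** The point holds at moderate weight. As stated, the model for the primary outcome cannot remove a shift between the ends of the two periods, and the article's own reasoning makes such a shift plausible. The likely harm is some loss of power and, when completers are unequal by sequence, a modest bias of unpredictable sign. At a drift of 5 μmol/L the effect is minor: power 0.88, and bias of at most 1.0 even at 18/12. At 20 the power loss at 15/15 is about 0.11.

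These sizes rest on three assumptions: a drift that the article does not give, 30 participants analysed with both period ends, and dropout unrelated to sequence for the probabilities. The second follows the article's missing-data rule, which drops participants lacking a required value and does not impute. The Background supports the direction of the drift but not its size. The change is therefore advisable and nearly free, but its absence would not invalidate the trial.

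**What to change.** In the Statistical analysis section, state the model for continuous outcomes in full: treatment, period, sequence and sex as fixed effects, with participant as the repeated or random unit. In MaAsLin, add period beside the participant random effect. No change to PERMANOVA is asked for on this point.

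The cost is a line of wording and one degree of freedom: with no drift and 15/15 completers, power goes from 0.888 to 0.887. At 18/12 with no drift, simulated power goes from about 0.89 to about 0.875. Make the change before unblinding, so that it is not a post hoc choice of model.

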#### Metabolomics

Serum, faecal, and urine samples will be collected at the end of run-in and treatment periods. The metabolomics analyses and informatics will be conducted by McMaster University in Hamilton, ON. Targeted analysis of water-soluble metabolite classes including amino acids, sugars, alcohols, organic acids, amines, TCA cycle intermediates, and short-chain fatty acids using quantitative NMR spectroscopy will be conducted on serum collected at the endpoint of each study period [24]. A targeted quantitative metabolomics approach will be used to analyse urine samples using a direct injection mass spectrometry with a reverse-phase LC-MS/MS assay. Serum and urine samples will be collected in accordance with metabolomic sample collection guidelines, allowing as much as possible that the original metabolic profile of the fresh samples is maintained and minimizing potential pre-analysis sample collection or handling issues that could bias the results of the metabolomic analyses [25].

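### A blanket p < 0.05 is the only significance criterion that reaches the metabolite-level tests, although the OTU associations are judged at q < 0.1

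*Protocol article*

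**What the plan says.** The last paragraph of the Statistical analysis section in the protocol article describes a mixed model for linear outcomes at the end of each period and then sets the threshold: "Statistical significance will be set at *p* < 0.05 for all analyses". The phrase allowing exceptions in that paragraph belongs to the preceding sentence, on reporting least-squares means with standard errors. It does not qualify the threshold.

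The paragraph before it, on the microbiome, has two more specific rules:

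- For the MaAsLin associations of core OTUs: "Significant associations will be considered below a *q*-value threshold of 0.1".
- In the text on α-diversity: "All pairwise comparisons among the groups will be tested using Tukey studentized range adjustment".

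The Metabolomics section plans work in several matrices: "Serum, faecal, and urine samples will be collected at the end of run-in and treatment periods". The serum NMR assay covers "water-soluble metabolite classes including amino acids, sugars, alcohols, organic acids, amines, TCA cycle intermediates, and short-chain fatty acids". For urine, "A targeted quantitative metabolomics approach will be used to analyse urine samples". Outcome measures and Sample handling also list faecal metabolomics, though no faecal assay is described. The article gives no number of metabolites, no metabolite-specific model and no rule for error control across metabolites.

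**The concern.** OTUs and metabolites are the two high-dimensional families in this trial. For OTUs the plan uses a false-discovery threshold. For metabolites the only criterion available is the general 0.05, and the article gives no reason for treating the two families differently.

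Applied metabolite by metabolite, a 0.05 threshold yields chance findings in proportion to the size of the panel. The measured classes include amino acids and short-chain fatty acids, which bear on the mechanism proposed in the Background and Discussion: less bacterial amino acid metabolism and more carbohydrate fermentation. The Discussion also says that the results will form the basis of a larger multicentre trial. A few chance hits in these classes could be taken as mechanistic support.

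**Working it through.** **The plan's own figure.** Sample size calculation gives n = 30, difference 17.5 μmol/L, SD 45 μmol/L, within-person correlation 0.79, two-sided alpha 0.05 and power 0.88.

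- SD of the within-person difference = 45 × √(2 × (1 − 0.79)) = 29.16 μmol/L.
- Noncentrality = 17.5 / (29.16 / √30) = 3.287.
- Power from the noncentral t = 0.888 with 29 degrees of freedom, or 0.887 with 28.

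This reproduces the stated 0.88. The 0.05 level is consistent for the primary test, and the point below does not touch it.

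**Which rule covers which tests.**

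| Tests | Criterion in the article |
|---|---|
| MaAsLin OTU associations | q < 0.1 |
| Pairwise group comparisons (α-diversity text) | Tukey adjustment across groups, not across variables |
| Linear outcomes by mixed model | p < 0.05 |
| Metabolite-level tests | only the general p < 0.05 |

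**Expected chance findings.** Assume m metabolites, none truly changed, each tested at 0.05. The expected number called significant is 0.05 × m. The count m is an assumption, shown as a range:

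- m = 40: 0.05 × 40 = 2.
- m = 150: 0.05 × 150 = 7.5.

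Correlation between metabolites does not alter this expectation. It does alter the chance of at least one false finding. Under independence that chance is 1 − 0.95^m. The correlated values come from 20,000 simulated replicates of equicorrelated two-sided z-tests.

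| Correlation | m = 40 | m = 150 |
|---|---|---|
| 0 | 87% | >99% |
| 0.5 | 57% | 86% |
| 0.8 | 27% | 40% |

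**Share of false claims when some effects are real.** Assume 10% of metabolites truly change and each has 80% power. With m = 100, false positives = 90 × 0.05 = 4.5 and true positives = 10 × 0.8 = 8. The false share is 4.5 / 12.5 = 36%. It is 54% if 5% truly change and 20% if 20% do.

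**Under q < 0.1.** Using Benjamini-Hochberg, which is an assumption because the article does not name the q-value method, the simulated chance of any false claim with no true effects is about 4% to 10% for one family over m = 40 to 150 and correlations 0 to 0.8. It is close to 10% under independence. If q is computed separately in serum, urine and faeces, that rate applies to each matrix. Over three independent matrices the chance of at least one false claim is up to 1 − 0.9³ = 27%.

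**The case against.** A reader might infer that the plan contradicts itself on OTUs, since an OTU with p = 0.03 and q = 0.4 passes one rule and fails the other. The document does not support that reading. The q-value rule directly follows the MaAsLin description, and the 0.05 sentence comes later, in a paragraph on linear outcomes. A specific rule stands beside a general default, and an analyst would apply q < 0.1 to MaAsLin. The wording only needs clarifying.

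A reader might also infer that the plan prescribes unadjusted p-values for every metabolite. It does not say that. The sentence gives a cut-off and is silent on adjustment, and Tukey-adjusted p-values are presumably compared with the same 0.05. No metabolite-level test is described, and the metabolomics informatics are placed with the laboratory. That metabolites fall under the linear outcomes is an inference. A statistical analysis plan that is not shown could add an adjustment.

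These points limit the finding without removing it. Detail left out of an article would be no finding, but here a threshold is stated for every analysis without exception. A later plan that judged metabolites by q < 0.1 would depart from that sentence.

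The exploratory label in Study design lowers the stakes but does not change the rule for calling a result significant. The OTU analyses belong to the same exploratory trial and still have a q-value threshold. Family-wise error is also a strict yardstick for an exploratory panel, so the expected count of false positives is the better measure of size.

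**Conclusion.** The point holds, as a minor one. As written, the general 0.05 is the only significance criterion that covers metabolite-level tests, while the comparable OTU family has a q-value rule. If 40 to 150 metabolites are tested, none truly changes and p is taken at face value, about 2 to 7.5 chance findings are expected. The metabolite count is assumed. The chance of at least one false finding depends heavily on the assumed correlation and should not be quoted as a single figure.

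Severity stays minor because metabolomics is not a named primary or secondary outcome, the trial is described as exploratory, and the primary test and its power are untouched.

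**What to change.** In the last paragraph of Statistical analysis, replace the words that extend the 0.05 threshold to all analyses with:

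> unless otherwise specified; the MaAsLin OTU associations are judged at q < 0.1 as stated above, and the metabolite-level RPS-versus-cornstarch tests are judged by a Benjamini-Hochberg q-value < 0.1 and reported as exploratory.

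Add whether the q-value is computed over all metabolites pooled or within each matrix. If it is within each matrix, state that error control applies per matrix and not to the three together. The MaAsLin family, which tests OTUs against the available metadata, stays as the plan defines it and is kept separate from faecal metabolites.

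The cost is one sentence and a routine calculation. The small downside is that fewer individual metabolites will be called significant.
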